## Background

Allergic rhinitis (AR) is an immunoglobulin E (IgE)-mediated immunologic inflammatory response of the nasal membrane after exposure to certain allergens which include pollens, dust mites, moulds, smoke, animal dander, air pollutants and occupational agents [1–3]. Patients with AR present with nasal symptoms such as sneezing, nasal itching, nasal congestion and a runny nose; which may be combined with non-nasal symptoms such as itchy and watery eyes, as well as an itchy and sore throat [2, 4]. AR has a high prevalence worldwide ranging from 10 to 30% of the population affected [5]. In Australia, AR is a common respiratory condition that affects approximately 20% of population and the cost of medication from the pharmacy suppliers increased from $107.8 million to $226.8 million between 2001 and 2010 [6, 7] . The troublesome nature of AR symptoms have a significant impact on patients’ quality of life such as work and school performance, sleep and mental health [2]. Moreover, AR has a high impact on asthma and is associated with rhinosinusitis and other comorbidities such as conjunctivitis and chronic cough [2, 6, 8].

Current management of AR includes allergen avoidance, pharmacotherapies (such as H_1_-antihistamines, corticosteroids, chromones, decongestants, anti-cholinergic drugs and anti-leukotrienes) and allergen-specific immunotherapy [2]. Most of the medications for AR are over-the-counter in Australia [6]. However, these medications are unable to provide full symptomatic relief and some of them are associated with undesirable side effects such as drowsiness and dryness in the nasal cavity. Systemic glucocorticosteroids cannot be used in the long term due to systemic side effects, such as suppressed immune system, osteoporosis, hypertension, diabetes, and especially impact on children’s growth [2, 3]. Those could be the major reasons for more and more patients with AR seeking help from complementary and alternative medicine including acupuncture [9].

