### Sample size

The sample size was calculated using the program G*Power 3.1.9 [20]. Due to the absence of a similar acupressure study, the sample size estimation was based on an acupuncture study [21] that is closest to our study as we feel that using the acupuncture study would produce the best possible estimates of effect size and sample size. The effect size estimate in this acupuncture study was based on the main outcome variable (i.e., total nasal symptom score) which is also used in our study. We have also inflated the estimated sample size to cater for a 10% dropout which normally occurs in studies involving acupuncture. The effect size estimate is 0.6505. To achieve 80% power at the significance level 0.05 we need 45 subjects per group taking into consideration a 10% dropout rate.

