### Recruitment

People who are interested in taking part in this trial will be provided with a Participant Information Sheet with Consent Form (PIS-CF) and asked to complete a general questionnaire and screening questionnaire if they agree with the PIS-CF. Written consent will be obtained from each participant by the investigators before an initial interview. The activities in the initial interview will include the allergen skin-prick test, a physical examination and a Chinese medicine differential diagnosis [22] to achieve an AR diagnosis. The participants meeting the inclusion criteria will enter the 2-week run-in period. During this period, every participant will be asked to conduct two sets of weekly baseline assessment including a 7-point scale symptom severity assessment form [23], a Rhinoconjunctivitis Quality of Life Questionnaire with Standardized Activities (RQLQs) [24] and a medication usage form. All baseline assessment forms will be submitted in the first intervention session. Figure 1 outlines the procedures of the clinical trial.

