### Randomization and blinding

To minimize bias, eligible participants will be randomized into either the specific acupressure treatment group or the non-specific acupressure control group with an allocation ratio of 1:1. Randomization will be conducted after baseline assessment using a computer program run by an independent researcher who is not directly involved in the trial. The randomization codes will be put into individually sealed opaque envelopes with sequel trial numbers. The sealed opaque envelopes contain the information on the location of specific or non-specific acupressure points for self-administered acupressure. Each participant will be asked to pick one sealed envelope from the pack of all the envelopes and pass it onto the registered acupuncturist. This acupuncturist is the only person who knows the participants’ group allocation in the trial. Neither the participants nor other investigators (such as data entry personnel and data analyst) will know the participants’ allocation to receive specific or non-specific acupressure treatment. The randomization codes and the allocation of the participants will be revealed once the RCT is completed. However, in the event of the need of this grouping information (e.g., a participant experiencing severe adverse events), the investigators will access the grouping data on the request of the physician. The relevant information will be documented in the participant’s case report form.

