### Data analysis

Statistical analyses will be performed by an independent statistician at RMIT University using IBM SPSS Statistics for Windows Version 25 software (IBM Corp., Armonk, NY, USA). The chi-square test will be used to assess differences between the two treatment groups on categorical variables such as characteristic and demographic data at baseline. The *t* test will be used to assess differences between the two treatment groups on the primary outcomes (nasal and non-nasal symptom scores, QoL, global assessment score as well as the total score of the four domains) and secondary outcome variables (RQLQs and relief medication scores) at the end of treatment and follow-up periods. All analyses will follow the intention-to-treat principle. The Worst-Case-Scenario method will be employed to deal with the missing data. That is, we will carry forward the worst possible outcomes for the missing data. Participants enrolled in the study with data from at least one treatment will be included for analysis. No interim analysis will be performed due to the short duration of the trial.

All comparisons will be two-tailed and *p* values < 0.05 will be considered as statistically significant. Subgroup analysis may be performed according to syndrome differential diagnosis of Chinese medicine, severity of symptoms or age group of participants.

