### Trial status

This protocol is version 1. The advertisement for the recruitment began in August 2017 after the ethics approval. It is anticipated that the recruitment will be completed by the end of June 2020. The recruitment is currently in progress.

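### The unadjusted t test at both time points gives up precision that baseline scores, and possibly season and sensitisation at end of follow-up, could recover

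*Protocol article*

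**What the plan says.** All statements are in the protocol article.

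- **Data analysis:** the *t* "test will be used to assess differences between the two treatment groups on the primary outcomes", and on the secondary scores, at the end of treatment and of follow-up. "All comparisons will be two-tailed". No covariate is named. The optional subgroups are Chinese-medicine syndrome, severity and age.
- **Trial design:** 2 weeks of run-in, 4 of intervention and 8 of follow-up. The last comparison is therefore about 12 weeks after baseline.
- **Trial status:** advertising began in August 2017. "It is anticipated that the recruitment will be completed by the end of June 2020".
- **Participants, Table 1:** a positive skin-prick test is required. No allergen and no seasonal or perennial type is specified.
- **Background:** the disease is described as a response to "exposure to certain allergens which include pollens, dust mites, moulds" and other agents.
- **Recruitment:** "The activities in the initial interview will include the allergen skin-prick test", and two weekly sets of baseline scores are collected during the run-in.
- **Randomization and blinding:** allocation is "with an allocation ratio of 1:1", with no stratification factor named.
- **Sample size:** a standardised effect of 0.6505 is taken from an acupuncture study, with no mean difference or SD shown. The requirement drawn from it reads: "To achieve 80% power at the significance level 0.05 we need 45 subjects per group taking into consideration a 10% dropout rate".

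**The concern.** A two-sample t test leaves all between-person variation in its error term. Part of that variation is predictable from facts known before treatment.

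The main one is the participant's own baseline score, which is measured twice and then not used in the comparison. A second may be allergen exposure. The article itself lists pollens beside dust mites and moulds, accepts any sensitisation, and recruits for nearly three years. At week 4 the baseline score is recent and should carry most of a participant's exposure level. At week 12 it is a season old, so for a pollen-sensitised participant it may describe a different exposure.

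What is at stake is power and the width of the confidence interval at the only two post-treatment time points named for testing, in a trial of about 40 evaluable participants per arm.

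**Working it through.** **1. The plan's own figure.** With d = 0.6505, two-sided alpha 0.05 and 80% power, the noncentral t gives 39 per group (power 0.810), and 39/0.9 = 43.3, so 44. The stated 45 is consistent with this, so the sample-size arithmetic is not at fault. Evaluable: 45 x 0.9 = 40.5, taken as 40 per arm. Unadjusted power at d = 0.6505 and 40 per arm is 0.819.

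**2. Assumptions not in the documents.** Effect 0.5 SD; total variance 1 without season; correlation 0.5 between a person's weekly scores; baseline the mean of two weeks; 60% pollen-sensitised; enrolment uniform over the year; a seasonal term of A x cos(date) for sensitised participants only. Its variance is v = 0.6 x A²/2 = 0.3A².

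**3. Baseline adjustment, no seasonality (A = 0).**
- t test: effective d = 0.5, power about 60%.
- Baseline variance = 0.5 + 0.5/2 = 0.75; covariance with outcome = 0.5; residual variance = 1 - 0.5²/0.75 = 0.667.
- Adjusted d = 0.5/√0.667 = 0.612, power about 77%.

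**4. Baseline adjustment, A = 0.8, week 12.**
- v = 0.3 x 0.64 = 0.192. t test: d = 0.5/√1.192 = 0.458, power about 52%.
- Seasonal correlation over 84 days: cos(2π x 84/365) = 0.124. Covariance = 0.5 + 0.192 x 0.124 = 0.524; baseline variance = 0.942.
- Residual variance = 1.192 - 0.524²/0.942 = 0.901; d = 0.5/√0.901 = 0.527, power about 64%.

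**5. Adding sensitisation, in/out of season and their product.** By simulation of the same model, approximate week-12 power:

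| Amplitude A (SD) | t test | Baseline only | Baseline + season terms | Change from season terms |
|---|---|---|---|---|
| 0 | 60% | 77% | 75% | -2 |
| 0.3 | 58% | 74% | 74% | -1 to 0 |
| 0.5 | 56% | 71% | 72% | +1 |
| 0.8 | 52% | 64% | 70% | +6 |
| 1.2 | 45% | 52% | 64% | +12 |

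At A = 0.8, 12 of the 18 points gained come from baseline and 6 from the season terms.

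**6. Week 4.** The seasonal correlation over 28 days is cos(2π x 28/365) = 0.886. At A = 0.8 the covariance is 0.5 + 0.192 x 0.886 = 0.670 and the residual variance is 1.192 - 0.670²/0.942 = 0.715, so d = 0.5/√0.715 = 0.591 and power is about 74%. In simulation the season terms move this by about 1 point or less at A = 0.8 and 1.2. Baseline alone is enough there.

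**7. At the planned effect.** With d = 0.6505 and A = 0.8 at week 12, the t test has 0.6505/√1.192 = 0.596, power 75%. Baseline adjustment gives about 85%, and the season terms about 89%. This treats seasonal variance as additional to the SD behind 0.6505. If that SD already contains it, the t test keeps its 82%.

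**8. Chance imbalance.** Suppose half of 45 per arm are enrolled in season under simple randomisation. The SD of the difference in proportions is √(0.25 x 2/45) = 0.105. A gap of 15 points or more is 0.15/0.105 = 1.42 SDs, with probability about 15%.

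**The case against.** **The test is valid.** Allocation is randomised, season and sensitisation balance in expectation, and the t test's standard error already allows for chance imbalance. This stands. A reader might infer that enrolling across seasons biases the result, or that the imbalance in step 8 is a defect of the plan. Neither follows. Type I error and unbiasedness are intact, and the issue is precision only.

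**Season is not shown to be a large source of variation.** The documents give no seasonal amplitude, no pollen-sensitised share and no within-person correlation. Below about 0.5 SD the season terms gain nothing useful beyond baseline. Continued medication, which the article allows, could also dampen swings. This stands, and it is why the gain is shown as a range that includes a loss.

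**Crossing a season boundary is not symptom change.** With uniform enrolment, 84/91.3 = 92% of participants end follow-up in a different calendar quarter from randomisation, against 28/91.3 = 31% at end of treatment. A reader might take the 92% as the size of the problem. It counts everyone, including those sensitised only to mites or dander, and says nothing about symptoms.

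**The skin-prick panel is not described.** A pollen yes/no variable may not be obtainable, and one set of season dates may not suit every pollen. This stands and makes that part of the fix conditional.

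**Covariates belong in the analysis plan, which is not shown.** This does not fully answer the point. The article does not leave the method open: it names a t test in the abstract and again under Data analysis.

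**Conclusion.** The point holds as one of efficiency. The named analysis is legitimate but discards information the trial collects.

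The firmer part is baseline adjustment at both time points: about 60% to 77% power with no seasonality, and at week 12 about 52% to 64% with a 0.8 SD amplitude. It rests on 40 per arm, a 0.5 SD effect and a within-person correlation of 0.5.

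The season and sensitisation terms are the weaker part. They matter only at end of follow-up, and their effect runs from about -2 to +12 points depending on an amplitude the documents do not give. A reader might conclude that the trial is underpowered because of season. The documents do not support that: the stated 45 per group reproduces, and whether its SD already includes seasonal variation depends on a cited study not at hand.

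**What to change.** In Data analysis, replace the t test at both time points with a linear model containing treatment and the baseline score (the mean of the two run-in assessments).

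For the end-of-follow-up comparison, also prespecify three terms: pollen sensitisation from the skin-prick test, if the panel identifies it; in or out of pollen season at the scheduled assessment date; and their product. Use the scheduled date, not the actual one. It is fixed by the randomisation date, so it is a valid pre-treatment covariate. Fix the season dates before unblinding. If the panel does not separate pollens, keep the baseline-only model.

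The cost is wording in the analysis plan, with no new data or visits. If symptoms prove not to be seasonal, the three extra terms cost about 2 power points against the baseline-only model (77% to 75%), which is still above the t test's 60% under the same assumptions.

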### Outcome measures

Primary and secondary outcome measures will be included in this clinical trial. The comparison between two groups will be at baseline, at the end of the treatment period and at the end of the follow-up period. The RCT schedule of recruitment, interventions and assessments is shown in Fig. 3.

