#### Primary outcome measures

The primary outcome measure will be AR symptomatic relief measured by a 7-point scale of symptom severity with the score ranging from 1 to 7. It contains four domains including I (nasal symptom severity), II (non-nasal symptom severity) and IV (quality-of-life assessment of rhinitis severity) where a higher score indicates more severe symptoms and better quality of life (QoL) as well as III (global assessment of nasal and non-nasal symptom severity) where a lower score indicates more severe symptoms [23]. The scores of four individual domains will be assessed separately at baseline and during the intervention period on a weekly basis and in the follow-up period on a fortnightly basis. The primary outcome of the intervention will be a combination of the four domains.

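### Five primary scores are each tested at two time points at an unadjusted 0.05, so the trial has no single success criterion and its false-positive rate is well above 5%

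*Protocol article*

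**What the plan says.** Four sections of the protocol article bear on this point.

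- **Data analysis.** This section refers to "primary outcomes (nasal and non-nasal symptom scores, QoL, global assessment score as well as the total score of the four domains". That is five scores: four domains and their total. The t "test will be used to assess differences between the two treatment groups on the primary outcomes", applied "at the end of treatment and follow-up periods". The decision rule covers everything: "All comparisons will be two-tailed" and p "values < 0.05 will be considered as statistically significant".
- **Primary outcome measures.** The four domains are scored separately, but "The primary outcome of the intervention will be a combination of the four domains".
- **Outcome measures.** "The comparison between two groups will be at baseline, at the end of the treatment period and at the end of the follow-up period". None of these times is singled out as primary.
- **Sample size.** "The effect size estimate is 0.6505". It comes from an acupuncture study's total nasal symptom score, which this section calls the main outcome variable. The calculation uses 80% power, one significance level of 0.05 and 10% dropout, and arrives at 45 per group.

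**The concern.** Three sections point to three different primary quantities: a single combination, five scores, and a nasal symptom score. None of them fixes the time at which the primary comparison is made. Under the Data analysis wording, ten results carry the primary label and each is called significant at 0.05. The article states no order of testing, no division of alpha and no requirement that all must succeed.

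The Background calls this a superiority trial. A report that follows this text could present any one of the ten results as a positive primary finding. The nominal 5% would then not be the error rate of the trial's main conclusion, and the sample size would support only one of the tests.

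**Working it through.** **1. The plan's own figure.** Inputs from Sample size: d = 0.6505, power 80%, alpha 0.05 (two-sided, from Data analysis), dropout 10%, two equal groups.

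- Two-sample t test (noncentral t): n = 38.08, so 39 per group. With dropout, 39/(1 − 0.10) = 43.3, so 44.
- Normal approximation: n = 2(1.960 + 0.842)²/0.6505² ≈ 37.1, so 38. With dropout, 38/0.90 = 42.2, so 43.

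Both are within two participants of the stated 45, so the figure reproduces. It holds for one test at 0.05.

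**2. Number of tests.** 5 scores × 2 time points = 10, each at 0.05.

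**3. Reference values under independence, 1 − 0.95^k.**

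- k = 10: 40.1%
- k = 5: 22.6%
- k = 2: 9.75%

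The 40.1% cannot actually occur, because the total is built from the four domains. It is only an upper reference.

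**4. Correlated tests.** The article gives no correlations, so those below are assumptions. Under the null hypothesis for all scores, 400,000 sets of z statistics were simulated for four domains at two times. One correlation was used between domains (ρ) and one between times (τ). All domains were assumed to point the same way with equal variance. The total at each time is the sum of its four domain statistics divided by √(4 + 12ρ). A set counts as a false positive if any |z| exceeds 1.96.

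| ρ | τ | Any of ten | Five scores, one time | Total only, two times |
|---|---|---|---|---|
| 0 | 0 | 36.6% | 20.3% | 9.8% |
| 0.3 | 0.5 | 30.8% | 18.0% | 9.1% |
| 0.5 | 0.5 | 27.2% | 15.9% | 9.1% |
| 0.7 | 0.7 | 21.0% | 13.1% | 8.3% |
| 0.9 | 0.9 | 13.0% | 9.4% | 7.1% |

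Counting only false positives that favour specific acupressure, any of ten gives 13.7% at ρ = τ = 0.5, 10.5% at 0.7 and 6.4% at 0.9. The nominal one-directional rate is 2.5%.

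**5. Cost of keeping every test and correcting by Bonferroni** (d = 0.6505, 80% power, t test). About 40 completers per group are expected, since 45 × 0.90 = 40.5.

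| Tests | Alpha each | Needed per group | With 10% dropout | Power with 40 per group |
|---|---|---|---|---|
| 1 | 0.05 | 39 | 44 | 82% |
| 2 | 0.025 | 47 | 53 | 73% |
| 5 | 0.01 | 57 | 64 | 61% |
| 10 | 0.005 | 65 | 73 | 51% |

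**The case against.** The best defence is that the section defining the outcomes ends with one combined primary outcome. The list in Data analysis could then be no more than the component scores of one instrument that will be t-tested. On that reading there is one primary score at two times, and the error rate is about 7% to 9% for between-time correlations of 0.9 to 0.5. That is a much smaller excess. It remains an excess, however, because no time point is chosen. The reading also has to set aside the plural primary label that Data analysis gives to all five scores.

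A second defence is that a condensed article may leave multiplicity to an analysis plan that is not shown, and that the article never says one significant result out of ten means success. It is true that no explicit success rule is stated. But the article does fix a list of primary scores, two test times and one significance rule for all comparisons, and these conflict with its own definition of the primary outcome. An analysis plan could follow that text faithfully and still leave ten primary tests at 0.05.

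Two cautions stand. The correlations are assumed, and high values pull the ten-test figure down to 13%. Also, treating the total nasal symptom score of the Sample size section as the nasal domain of the 7-point scale is an inference; the article says only that the score is also used in this trial.

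**Conclusion.** The point holds; the plan is wrong as written. With ten tests at 0.05, the chance of at least one false-positive primary result is about 21% to 31% for domain correlations of 0.3 to 0.7 and time correlations of 0.5 to 0.7. It ranges from 13% to 37% over all correlations tried, from 0.9 down to 0. Five scores at a single time give about 13% to 18% for domain correlations of 0.7 to 0.3. The most favourable reading, the combined score alone at two times, gives about 7% to 9%. No reading of the text holds the level at 5%.

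The exact sizes depend on the assumed correlations and on four equally weighted, aligned domains. The excess over 5% does not. The contradiction between the sections needs no calculation.

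**What to change.** Name one primary score at one time point, and use identical wording in Outcome measures, Primary outcome measures, Sample size and Data analysis. Either of these would do:

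- **Nasal symptom domain at the end of the 4-week treatment period.** If this domain is the score behind the effect size, 45 per group stands. The article should say so.
- **The combined score already named in Primary outcome measures, at one stated time.** This changes the declared outcome least. The effect size of 0.6505 comes from a nasal score, so its use for the combination would need a sentence of justification.

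Make the remaining domains, the other candidate score and the other time point secondary. Test them in a stated fixed order or with Holm. If several scores or both times must stay primary, state the multiplicity procedure and redo the sample size. Under Bonferroni this means 53 per group for two tests, 64 for five and 73 for ten.

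The cost is a protocol and analysis-plan amendment and a registry update. Recruitment began in August 2017 and was still in progress, so the amendment should give its reasons and record that it was made before any outcome data were seen by group. The only loss is that the other scores give up primary status.

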#### Secondary outcome measures

The secondary outcome measures will consist of the RQLQs [24], relief medication scores, adverse events and participants’ opinion about this clinical trial. The RQLQs is used to assess the patient’s quality of life and daily activities which contain seven domains with scores from 0 to 6; a higher score indicates a more severe impact on QoL [24]. The use of anti-allergic medication is calculated as each daily dose of antihistamines or decongestant nasal spray or eye drops was equivalent to 1 point; orally administered antihistamines as 2 points and a steroid nasal spray or eye drops as 3 points [26]. If the participants use orally administered corticosteroids or acupuncture for AR during the trial period, they will be asked to discontinue the self-administered acupressure treatment and considered as withdrawing from this study. Adverse events will be self-monitored and recorded in the adverse events form. If there are severe adverse events from the self-administered acupressure, the relevant participants will be asked to terminate the study and contact the researchers immediately. They will be referred to general practitioners or the emergency department for management. All severe adverse events will be investigated and reported in writing to the RMIT HREC immediately. A questionnaire will be used to seek participants’ opinion on the expectancy of self-administered acupressure for AR and the credibility of the blinding method used in the study.

RQLQs and relief medication scores will be assessed at baseline, intervention period (weekly) and follow-up period (fortnightly). Acupressure dosage and adverse events will be recorded in a weekly form during the treatment period to monitor participants’ compliance and safety, and adverse events will be further assessed fortnightly in the follow-up period. Participants’ opinion will be assessed at the end of first and final weeks of the intervention period.

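### Worst-possible-outcome imputation has no unique value for the relief medication score, which has no stated maximum, and the choice of ceiling changes that comparison materially

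*Protocol article*

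**What the plan says.** The Data analysis section of the protocol article fixes one missing-data method for the trial: "we will carry forward the worst possible outcomes for the missing data". The same paragraph names the t test for the primary outcomes and for "secondary outcome variables (RQLQs and relief medication scores) at the end of treatment and follow-up periods". No outcome is exempted. Participants with data from at least one treatment are to be analysed.

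The outcomes differ in whether they have an end point:

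- Primary outcome measures describes "a 7-point scale of symptom severity with the score ranging from 1 to 7".
- Secondary outcome measures gives the RQLQs domains a range of 0 to 6.
- The same section builds the medication score from doses: "each daily dose of antihistamines or decongestant nasal spray or eye drops was equivalent to 1 point; orally administered antihistamines as 2 points". Topical steroid products score 3. It states no limit on doses, products, days or the total.

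The protocol expects missing data. Sample size says "we need 45 subjects per group taking into consideration a 10% dropout rate". Secondary outcome measures adds that users of oral corticosteroids or acupuncture for AR are "considered as withdrawing from this study", and that severe adverse events from the acupressure lead to termination. Oral corticosteroids have no point value in the score.

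**The concern.** A worst possible value can be read off a scale with end points. It cannot be read off an open-ended sum of points per dose. For the relief medication score, the rule tells the analyst to impute a value that the protocol does not identify.

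At least three readings are open. One is the participant's own worst recorded score. Another is one dose of each point class per day. A third is some larger ceiling. They can lead to very different imputed values.

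This score is the only outcome listed that measures the exploratory aim, stated in the Background, of reducing Western medication use. If the value is settled after the data are seen, a choice made by the analyst enters the mean difference and the standard deviation of the t test. The bounded outcomes do not share this problem.

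**Working it through.** **1. The plan's own figure.** With d = 0.6505, two-sided alpha 0.05 and 80% power, the exact t calculation gives 38.08, so 39 per group. Then 39/0.9 = 43.3, so 44. A rank-test allowance gives 40, and 40/0.9 = 44.4, so 45. The stated 45 per group is reproduced to within one or two participants and is not in question. The 0.6505 comes from a nasal symptom score, not from the medication score.

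**2. How many values are imputed.** 10% of 45 is 4.5, so about 4 to 5 per arm on the planning figure.

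**3. Candidate ceilings.** One dose of each point class per day gives 1 + 2 + 3 = 6 points a day, or 6 × 7 = 42 a week. Two doses of each give 12 a day, or 84 a week. Both are readings tried here; neither is stated in the document.

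**4. Assumptions.** The document gives no mean, SD or distribution for this score. Assumed: gamma-distributed weekly scores, control mean 14, SD 10, and a true difference of 0.6505 × 10 = 6.505 points. There are 45 per arm, and each participant is missing at random with probability 4/45 = 0.089.

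**5. Power by formula.** If a fraction p is set to a ceiling C, the arm variance becomes (1 − p)σ² + p(1 − p)(C − μ)², and the true difference shrinks by the factor (1 − p). Here p(1 − p) = 0.081, and the diluted difference is 0.911 × 6.505 = 5.93.

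| | C = 42 | C = 84 |
|---|---|---|
| Control variance (μ = 14) | 91.1 + 0.081 × 28² = 154.6 | 91.1 + 0.081 × 70² = 488 |
| Treated variance (μ = 7.495) | 91.1 + 0.081 × 34.5² = 187.5 | 91.1 + 0.081 × 76.5² = 565 |
| Pooled SD | 13.1 | 22.9 |
| Standardised difference | 5.93/13.1 = 0.45 | 5.93/22.9 = 0.26 |

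**6. Power by simulation** (20,000 runs, two-sided t test):

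| Handling of missing values | Power |
|---|---|
| Omitted | about 83% |
| Ceiling 42 a week | about 57% |
| Ceiling 84 a week | about 25% |

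With no true effect and equal dropout rates, the two-sided type I error stays near 5% under each ceiling.

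**7. Unequal dropout, no true effect.** With 15% missing in one arm and 5% in the other, the expected spurious difference is (0.15 − 0.05) × (C − 14).

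- C = 42: 0.10 × 28 = 2.8 points
- C = 84: 0.10 × 70 = 7.0 points

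In simulation, significance against the higher-dropout arm occurs in about 18% (C = 42) to 29% (C = 84) of trials, against a nominal 2.5% in that direction. With missing values omitted there is no such bias when dropout is unrelated to the score.

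**8. Sensitivity to the assumed SD.** With SD 7, 10% random dropout in each arm and a true difference of 0.65 SD, power is 76%, 41%, 14% and 9% for ceilings of 21, 42, 84 and 126 a week. Under 5% against 15% dropout, one-directional false significance is 7%, 22%, 32% and 35%. The pattern is the same.

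**The case against.** The strongest reply is that the rule can be given a value. To carry forward may mean the participant's own worst recorded score, which the baseline, weekly and fortnightly forms would usually supply. A daily dose may be meant to count once per class per day, which caps the score at 6 a day. The scoring method is cited to an outside source that may contain a cap, and an unseen analysis plan may define the value. This stands to the extent that the rule is ambiguous rather than impossible to apply. It does not remove the point. The article fixes the method, the text does not choose between the readings, and even the 6-a-day reading cuts power from about 83% to 57% under the assumptions above.

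A reader might infer that power could collapse to a few percent. Figures that low (3% at a ceiling of 84) arise only if exactly four participants are missing in each arm, so that the imputed values inflate the SD but never differ between arms. Random dropout at the same average rate gives about 25%.

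A reader might also infer that the ceiling produces false positives in general. It does not when dropout rates are equal. The 15% against 5% split is an illustration, and nothing in the document predicts it.

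Finally, the reach is limited. The affected outcome is secondary, it serves an exploratory aim, and the trial is not powered on it. The 10% is a planning figure, and participants without data from at least one treatment are left out, so fewer values may be imputed.

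**Conclusion.** The point holds in a limited form. The protocol article applies one worst-possible-outcome rule to every tested outcome, and for the relief medication score that rule yields no unique value. The candidate ceilings of 42 and 84 points a week reduce power from about 83% to about 57% and 25%. Under markedly unequal dropout they add 2.8 to 7.0 points of bias. All these sizes rest on the assumed mean, SD, distribution and dropout pattern, and only the direction and the mechanism follow from the document itself. The own-worst-recorded reading was not quantified.

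The document does not support saying that the medication score cannot be analysed at all, that an arbitrary ceiling decides the trial's result, or that the primary scale or the RQLQs share this defect. Their ranges are finite. Whether worst-case imputation suits them is a separate matter.

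**What to change.** In Data analysis, exempt the relief medication score from the worst-possible-value rule. Express it as mean points per day, so that weekly and fortnightly records are on one scale. Analyse it with a mixed model for repeated measures, or with multiple imputation by arm, using the baseline, weekly and fortnightly scores already collected. If a worst-case version is wanted, keep it as a sensitivity analysis with one numerical ceiling in points per day, fixed before unblinding.

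A single sentence defining the worst value would remove the ambiguity, but it would leave the loss of power and the sensitivity to unequal dropout in place.

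The cost is a wording change and a little more analysis, with no new data or participants. The article reports recruitment as still in progress. The downside is that the main analysis of this score then relies on data being missing at random. That is open to doubt for participants withdrawn because of the treatment they used, and the fixed-ceiling sensitivity analysis probes it.
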